## Criteria for Suspension of Study

CDC has the right to terminate this study at any time. Reasons for terminating the study may include the following:

1. The incidence or severity of adverse events in this or other studies indicate a potential health hazard to participants
2. Enrollment and/or compliance is unsatisfactory
3. Data recording is inaccurate or incomplete
4. Recommendation by the safety review team

If the study is discontinued before the planned end due to clinical health concerns, each participant remaining in the study at that point will be seen for a final follow-up visit scheduled one month after the last study product had been dispensed. Adverse events, STI, and HIV infections detected through this follow-up visit will be included in the analysis.

## Unblinding

Within 9 months after study database is locked and analysis completed, study staff will receive participant treatment assignment. Participants will be contacted by telephone to be notified of their treatment assignment and be updated on the results of the study.

# STUDY PROCEDURES FOR PARTICIPANTS DIAGNOSED WITH HIV INFECTION (PART B)

In spite of intensive prevention education and risk reduction counseling, it is possible that some participants will become infected with HIV while participating in the study.

Confirmed HIV infection will be defined as the following:

- HIV RNA PCR ≥ 5000 copies/ml on two separate occasions in the setting of a negative HIV EIA antibody test and negative or indeterminate WB or IFA (acute infection)
- Positive HIV EIA antibody test and confirmatory WB or IFA

Participants who have a reactive HIV rapid test or present with a history of a positive HIV test at any time during the study will have confirmatory testing by both a HIV EIA antibody and WB or IFA and RNA PCR (if indicated). Study product will be held for a reactive HIV antibody test. If HIV infection is confirmed, study product will be permanently discontinued.

Participants who develop confirmed HIV-1 infection after enrollment into the study will be discontinued from study product and complete an early termination visit from the main protocol (Part A). They will be referred for medical and psychosocial care. They will be asked to continue in the study (Part B) and be scheduled for study visits at 1, 3, 6, 9, and 12 months after diagnosis of HIV infection (Table 3 – Appendix 3). The termination visit for Part A may also serve as the baseline visit for Part B, with the addition of HIV-specific labs or a separate visit may be scheduled. Following HIV diagnosis, follow-up telephone calls will be made at weeks 1 and 2 according to site-specific procedures and participant request for the purpose of support, referrals, education, and counseling.

## Baseline Visit

The following procedures are to be performed at the time of HIV diagnosis:

Clinical assessment:

- Complete Physical Examination
- Adverse Event/HIV-related Medical History
- Concomitant Medication Form

*Laboratory assessment:*

- HIV EIA Antibody and WB/IFA testing accompanied by risk reduction counseling
- HIV-related tests
  - CD4+ cell count
  - Genotypic and phenotypic resistance testing
  - Viral load by RNA PCR assay (Roche Amplicor Version 1.5)
- Laboratory tests (to be performed if > 2 weeks since last test performed)
  - STI testing
    - Urine for GC and CT
    - RPR
- Chemistry profile
- Urinalysis
- Hematology profile
- DEXA scan
- Blood sample for storage
- Plasma
- PBMCs

## Follow-up Visits

HIV-infected participants will be scheduled for follow-up visits at 1, 3, 6, 9, and 12 months after their baseline visit to assess for antiretroviral resistance and viral setpoints. Study visits are to be completed + 7 days for the month 1 visit and within + 14 days for the remaining protocol-related visit dates based on the enrollment visit date.

The following procedures are to be performed at each follow-up visit unless otherwise specified:

Clinical assessment:

- Symptom-directed Physical Examination
- Concomitant Medication Form
- Adverse event (for events reported during Part A)/Intercurrent Illnesses (new HIV-specific intercurrent illnesses) Form
- HIV risk reduction counseling

*Laboratory assessment:*

- Urinalysis, Hematology and Chemistry Profiles (only if necessary for continuation of AE monitoring from event reported during Part A)
- Viral load by RNA PCR assay (Roche Amplicor Version 1.5)
- CD4+ cell count
- Genotyping[[2]](#footnote-3)
- Blood samples for storage
- Plasma
- PBMCs

After participants complete all scheduled study visits, they will be contacted periodically until final study closeout. The purpose of these interim contacts will be to update contact information and to inform participants of the progress of and timeline for completing the study.

# DATA SOURCES

## Study eligibility assessment

Participants will undergo brief face-to-face interviews at the screening and enrollment study visits by trained study staff. The screening interviews will obtain information on demographics, behavioral risk, and study eligibility criteria.

## Clinical assessment

A symptom-driven physical examination will be performed at screening and a complete physical exam at enrollment by a trained healthcare provider. Clinical symptoms will be systematically assessed in a structured medical interview at 1, 3, 6, 9, 12, 15, 18, 21, and 24 months for the immediate treatment arms, and at 1, 3, 6, 9, 10, 12, 15, 18, 21, and 24 months for the delayed treatment arms. The severity of clinical symptoms will be scored using the established National Institutes of Allergy and Infectious Diseases (NIAID) Division of AIDS (DAIDS) toxicity scale (Appendix 7). Additional data will be collected regarding concomitant medication use.

Telephone interviews will be performed by trained study staff to identify any potential adverse events or adherence issues at 2 and 8 weeks following enrollment for the immediate treatment arms, and at 38 and 44 weeks for the delayed treatment arms.

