# STUDY DESIGN

This protocol describes a randomized, double-blind, placebo-controlled three-site study to evaluate the safety and tolerability of daily oral TDF among HIV-1 negative MSM.

Four hundred healthy, HIV‑1‑negative MSM will be randomized to one of four treatment arms:

Group 1: TDF 300 mg po QD

Group 2: Placebo po QD

Group 3: No study product for 9 months, followed by TDF 300 mg po QD

Group 4: No study product for 9 months, followed by placebo po QD

Groups 1 and 2 will be referred to as the immediate treatment arms and will receive study product for the entire 24 months of the study. Groups 3 and 4 will be referred to as the delayed treatment arms, and will receive study product starting at 9 months and ending at 24 months, for a total duration of 15 months on study product. For the purposes of this study, a month is considered 30 days. Participants will be stratified by enrollment site.

Participants will be monitored for clinical safety using periodic physical examinations, adverse event reporting, and serial laboratory testing. Given the uncertainty regarding the clinical significance of whole-body duel-energy x-ray absorptiometry [DEXA] findings and their lack of correlation with other clinical data (e.g. fractures), SFDPH site participants will receive DEXA scans at screening and two follow-up visits (at 12 and 24 months in the immediate arm, at 9 and 24 months in the delayed arm), and at the time of study discontinuation, if at least 6 months has passed since the previous scan. Behavioral safety will be primarily assessed by comparing reported risk behaviors between the immediate (pill-groups 1 and 2) and delayed (no pill-groups 3 and 4) treatment arms and will be evaluated by the use of periodic risk behavior assessments via audio computer-assisted self interview (ACASI) and regular laboratory testing for HIV and sexually transmitted infections (STI) including syphilis, *Neisseria gonorrhoeae* (GC), and Chlamydia trachomatis (CT). Additionally, measurements of adherence will be evaluated to determine product acceptability.

Study Schema

R

A

N

D

O

M

I

Z

E

Daily TDF

Daily Placebo

No treatment for 9 months, then daily TDF

No treatment for 9 months, then daily Placebo

Site B

Site A

Site C

Anticipated Timeline

Months

|  | 0-6 | | 7-12 | | | | 13-18 | | | 19-24 | | 25-30 | 31-36 | | 37-42 | |
| --- | --- | --- | --- | --- | --- | --- | --- | --- | --- | --- | --- | --- | --- | --- | --- | --- |

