# TREATMENT PLAN AND STUDY PRODUCT

## Treatment Plan

Participants will be assigned a participant number at the time of screening consent. Once eligibility has been confirmed, the site will be given a specific numeric identifier that corresponds to the product assignment. All screening and baseline tests and procedures must be completed prior to the receipt of the first dose of study product. Initiation of treatment with study product must take place within 24 hours after product dispensation.

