# MAIN STUDY PROCEDURES (PART A)

The study procedures to be conducted for each participant enrolled in the main study (Part A) are presented in Tables 1 and 2 (Appendix 3) and detailed in the text that follows. Participants who become HIV-I infected during the course of the study will be asked to continue under a separate visit schedule, referred to as Part B, presented in Table 3 (Appendix 3) that will be covered in Section 7. All routine laboratory specimens will be sent to local institutional laboratories for analysis. Other laboratory specimens will be sent to a designated central lab for analysis or storage.

Any deviation from protocol procedures should be noted in the Case Report Forms (CRFs) or the participant file and the CDC or Contract Research Organization (CRO) should be notified depending on the nature of the deviation.

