## Product administration

Each participant will be randomly assigned a unique ID number that corresponds to a pre-labeled, blinded, bottle of study product (TDF or placebo) tablets. At the enrollment visit for the immediate treatment arms and at the 9 month visit for the delayed treatment arms, participants will receive 37 tablets. They must return within 1 month after initial product receipt for a safety visit before receiving further study product. At the 1 month (immediate arm) and 10 month (delayed arm) visits participants will **have any returned pills re-dispensed and will** receive **an additional** 68 tablets. At subsequent quarterly visits, participants will receive 105 tablets.

Participants will be instructed to orally self-administer one tablet daily. The tablet should be swallowed whole. It is important to take the tablets regularly. Each dose should be taken as close as possible to twenty-four hours apart at the same time each day.

The participant will be counseled regarding signs and symptoms of toxicity and the importance of adherence. Two weeks and two months after the enrollment visit for the immediate arms and at 9.5 and 11 months for the delayed arms, participants will receive a phone call from study staff to assess any immediate problems. In addition, participants will be encouraged to call for any adverse experiences possibly related to study product, all serious adverse events, symptoms of acute retroviral infection or concerns regarding product adherence. Participants will be instructed to return unused study medication at each study visit and about the correct use of the MEMS® cap. Participants should not share or dispense study product to any other persons.

Dosage Modification

No modification of dosage will be allowed from this study. If a dose is forgotten, it should be taken as soon as remembered on that same day that it was missed. If a daily dose is missed, the participant should not double the dose the next day.

*Adherence Reminder Sessions*

Face-to-face adherence reminder sessions will take place at the initial product dispensing and each study visit thereafter. This session will include:

- The importance of following study guidelines for adherence to once daily study product
- Instructions about taking study pills including dose timing, storage, and importance of taking pills whole, and what to do in the event of a missed dose.
- Instructions about the purpose, use, and care of the MEMS® cap and bottle

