## Telephone Calls

Once participants receive study product, either at the enrollment visit (immediate arms) or at their 9 month visit (delayed arms) they will arrange with study staff for a scheduled telephone call at 2 weeks and 2 months following study product initiation to report any potential study-related symptoms or problems. If the symptoms resulted in the participant choosing to discontinue study product or require further clinical assessment, the participant will be requested to return promptly to the study site for evaluation and to return unused study product.

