## Follow-up Visits

Participants assigned to the immediate treatment arms will be scheduled for follow-up visits at 1 and 3 months after enrollment and then at months 6, 9, 12, 15, 18, 21, and 24 (Table 1, Appendix 3). Study visits for participants assigned to the immediate treatment arm are to be completed + 7 days based on the enrollment visit date. Participants assigned to the delayed treatment arms will be scheduled for follow-up visits at 1 and 3 months after enrollment and then at months 6, 9, 10, 12, 15, 18, 21, and 24 (Table 2, Appendix 3). Study visits for participants assigned to the delayed treatment arm are to be completed + 7 days based on their enrollment visit until their initial dispensing visit . After the initial dispensing visit (month 9), study visits for participants assigned to the delayed treatment arm will be completed + 7 days based on their month 9 visit date. Regularly scheduled evaluations will be made on all participants whether or not they continue to receive study product.

The following procedures are to be performed at all visits unless otherwise specified:

*Epidemiologic/Behavioral Risk Assessment*

- ACASI (3, 6, 9, 12, 15, 18, 21, and 24 months)

Clinical assessment

- Symptom-directed physical examination
- Administration of Adverse Events/Intercurrent Illness Form
- Concomitant Medication Form

*Laboratory assessment:*

- Hematology profile
- Chemistry profile
- Urinalysis
- Blood sample for storage
- Plasma
- Peripheral Blood Mononuclear Cells (PBMCs) (12 months for immediate treatment arms, 21 months for delayed treatment arms only)
- HIV-1 rapid whole blood EIA (3, 6, 9, 12, 15, 18, 21, and 24 months)
- DEXA scan **(SFDPH only: 12 and 24 months for immediate treatment arms, 9 and 24 months for the delayed treatment arms)**
- STI testing
- RPR (12 and 24 months)
- Urine for GC and CT (6, 12, 18, and 24 months)

Standardized HIV risk reduction counseling as per enrollment visit

During the 24 months of the study, additional HIV testing may be requested at any time by study participants, or may be performed as required by the protocol in the case of an indeterminate result or to help determine the timing of HIV infection more precisely.

After participants complete all scheduled study visits, they will be contacted periodically until final study closeout. The purpose of these interim contacts will be to update contact information and to inform participants of the progress of and timeline for completing the study.

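### Section 8.2 times the delayed-arm telephone calls at weeks 38 and 44, nominally 4 days before and 38 days after product start, which contradicts sections 6.4 and 6.7 (minor inconsistency)

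*Protocol*

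**What the plan says.** Three sections of the protocol time the delayed-arm telephone calls.

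- Section 8.2 (Clinical assessment) puts them "at 38 and 44 weeks for the delayed treatment arms". Their purpose there is to pick up possible adverse events or adherence issues. For the immediate arms the same sentence gives 2 and 8 weeks after enrollment.
- Section 6.4 (Product administration) puts them "at 9.5 and 11 months for the delayed arms".
- Section 6.7 (Telephone Calls) describes, for both sets of arms, a "scheduled telephone call at 2 weeks and 2 months following study product initiation".

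Four other statements fix the calendar.

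- Section 3 (Study Design): "For the purposes of this study, a month is considered 30 days". The same section starts product in the delayed arms at 9 months.
- Section 5.1 (Treatment Plan): "Initiation of treatment with study product must take place within 24 hours after product dispensation".
- Section 6.8 (Follow-up Visits) gives a 7-day window and, once product has been dispensed, dates delayed-arm visits "based on their month 9 visit date".
- Section 6.4, on the first supply of tablets: "They must return within 1 month after initial product receipt for a safety visit before receiving further study product".

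**The concern.** The calls exist to catch early problems once a man has started taking tablets. Section 8.2 counts them in weeks from enrollment, and its first week number falls just short of nine 30-day months. A call then cannot detect an adverse event arising on product, or a missed dose, because no tablet has yet been dispensed.

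What is at stake is the early on-product contact schedule in the delayed arms, which are half of the 400 men. Section 10.5 promises close monitoring over the first 8 weeks after dispensing. Under the 8.2 times, a man's first scheduled contact after his first tablet would be the month 10 visit. The immediate arms would still get their first call two weeks in.

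**Working it through.** **Inputs.** Month = 30 days and delayed-arm start at month 9 (section 3). First dose within 24 hours of dispensing (5.1). Calls at weeks 38 and 44 (8.2), at months 9.5 and 11 (6.4), and at 2 weeks and 2 months after start (6.7). Visit window of 7 days (6.8).

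**Nominal product start.** 9 × 30 = day 270, and 270 / 7 = week 38.6.

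**Call days, and offset from day 270.**

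| Source | First call | Second call |
| --- | --- | --- |
| 8.2 | 38 × 7 = day 266 (−4) | 44 × 7 = day 308 (+38) |
| 6.4 | 9.5 × 30 = day 285 (+15) | 11 × 30 = day 330 (+60) |
| 6.7 | 270 + 14 = day 284 (+14) | 270 + 60 = day 330 (+60) |

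In weeks, the 6.4 and 6.7 calls fall at 284 / 7 = 40.6 or 285 / 7 = 40.7, and at 330 / 7 = 47.1: about weeks 41 and 47.

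**Discrepancy.** First call: 284 − 266 = 18 days, or 285 − 266 = 19 days, too early. Second call: 330 − 308 = 22 days too early.

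**Can another reading rescue 8.2?**

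- *Calendar months.* 9 × 30.44 = day 273.9, and 266 − 273.9 = −7.9. The first call moves further ahead of the first dose.
- *Visit window.* If the printed + 7 days stands for plus or minus 7, dispensing falls on days 263 to 277. The week 38 call is then between 266 − 263 = 3 days after dispensing and 277 − 266 = 11 days before it. It is never a two-week call. Read literally as plus 7 only, dispensing falls on days 270 to 277 and the call is always 4 to 11 days before it.
- *28-day month.* 9 × 28 = day 252 = week 36, and 36 + 2 = 38 and 36 + 8 = 44. This reproduces both figures, but section 3 rules it out. Day 252 is 18 days before day 270 and 11 days before the earliest day of a plus-or-minus window.

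The exact match to 36 + 2 and 36 + 8 suggests that nine months was converted as 36 weeks. That origin is an inference. For the immediate arms the same conversion costs little: 8 × 7 = day 56 against 2 × 30 = day 60, or 4 days.

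**Scheduled contacts after dispensing, to month 12.** Months 10 and 12 are +30 and +90 days.

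- Using the 6.7 calls: +14, +30, +60, +90. First contact at +14; longest gap 30 days.
- Using the 8.2 calls: +30, +38, +90. First contact at +30; longest gap 90 − 38 = 52 days.

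Within the 8 weeks (56 days) of section 10.5, each schedule has two contacts. With the 8.2 times, none of them falls before +30.

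**The case against.** The best defence is that the rest of the protocol already gives the right answer. The opening of section 6 says that Part A procedures "are presented in Tables 1 and 2 (Appendix 3) and detailed in the text that follows", so section 6 is the detailed procedure text, while 8.2 sits in a descriptive chapter on data sources. Under 6.7 the call is arranged once the man has received product, so staff following it could not book a call before dispensing. Section 6.4 independently agrees, and 10.5 also counts close monitoring from dispensing. Other safeguards remain: counselling on toxicity and adherence at dispensing, encouragement to telephone with problems, and the month 10 safety visit before more tablets. All of this stands, and it keeps the point minor. It does not make 8.2 correct: as written, that section gives a different and unusable time for a safety contact.

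Three stronger readings are tempting, and the documents do not support them.

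- *A call before the first dose can find nothing.* Section 9.1 records adverse events with onset after the enrollment visit, including time off product, so such a call could identify a recordable event. It could not identify one arising on product, or an adherence problem.
- *Delayed-arm men will go without contact for their first month on product.* That happens only if a site follows 8.2 over 6.4 and 6.7, and nothing in the protocol suggests that sites would. The Appendix 3 schedule tables are not shown, so whether they repeat the error is unknown.
- *The safety comparison is biased.* TDF and placebo men in the delayed arms share the same call schedule, so the randomized contrast is unaffected.

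**Conclusion.** The inconsistency is real, and section 8.2 is wrong as written. This rests on the protocol's own 30-day month and month 9 start, and it survives the visit window and calendar months.

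The consequence is small and conditional. If a site scheduled from 8.2, its delayed-arm men would lose the two-week on-product call, wait until month 10 for their first scheduled contact after starting, and then have a 52-day gap before month 12. The ceiling is 400 / 2 = 200 men if every site did so, or 160 to 180 if all of the expected 10-20% loss occurred before month 9. If sites work from section 6, nobody is affected. No endpoint, estimate or TDF-placebo contrast changes in either case. This is a scheduling inconsistency worth correcting, not a flaw in the design.

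**What to change.** In section 8.2, replace "at 38 and 44 weeks for the delayed treatment arms" with: *2 weeks and 2 months after the initial dispensing visit (month 9) for the delayed treatment arms*. This matches 6.7. Anchoring to dispensing is better than substituting weeks 41 and 47, because 6.8 re-dates the later delayed-arm visits from the actual month 9 visit, and a call fixed in study weeks would drift against the first dose. If the Appendix 3 table for the delayed arm carries the same week numbers, it should be changed too.

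Changing the immediate-arm 8 weeks to 2 months would make the wording uniform but is optional.

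The cost is one phrase. It adds no visits, calls or tests.

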## Toxicity monitoring

Blood will be obtained at screening, enrollment and then at each subsequent study visit for toxicity monitoring. Routine toxicity monitoring will consist of the following laboratory tests: hematologic profile, chemistry profile, and urinalysis. DEXA scans will be used for a subset of participants. The severity of laboratory toxicity will be assessed and scored according to established laboratory toxicity scales (Gilead Sciences, Inc. toxicity scale for creatinine and DAIDS toxicity scale for all other laboratory toxicity monitoring [Appendix 7]).

